**Figure 3 F3:**
[figure not shown]
Consort diagram.

### Data analysis

2.5

We will use descriptive statistics to describe the sample (i.e., means, standard deviations, and percentages). To study the outcomes of the FGs, we will use a deductive content approach to synthetize the information. After transcribing the sessions, they will be coded, and results extracted and summarized. To study intervention effects, we will perform repeated measures ANOVAs, as described in section 2.3. Effect sizes will be estimated using partial eta squared (*η*ₚ²) for the repeated measures ANOVA, which is recommended for within-subjects designs. In cases where pairwise comparisons are conducted, Cohen's d will be reported to facilitate interpretation of the magnitude of differences. The analysis will follow and intent-to-treat approach, including all participants who initiated the digital treatment, regardless of their level of adherence to the protocol. For handling missing data, multiple imputation methods will be employed to account for potential biases and ensure the robustness of the results. The software IBM SPSS Statistics for Windows will be used.

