### Objectives

1.1

The overarching objective of this project is to help reduce the pain impact in adolescents with chronic pain and improve their functioning. We aim to achieve this by developing and implementing DigiDOL-Ad, a novel and reliable digital treatment (i.e., mobile application). With DigiDOL-Ad we aim to empower patients to better manage and cope with their chronic pain. In addition, this new app will be complemented by websites with resources and information, one specifically developed for parents or main caregivers and another for teachers. This article describes the protocol created for this project and follows the Standard Protocol Items: Recommendations For Interventional Trials (SPIRIT) guidelines (25) (see Supplementary Appendix 1 for the WHO Trial Registration Data Set information).

In pursuit of this goal, the project will evolve with specific objectives:
1.Improve the understanding of the needs of all stakeholders—adolescents with chronic pain, their parents/tutors, attending physicians, teachers, and health authorities—regarding the management of chronic pain and the features of DigiDOL-Ad. We expect to find many important, specific to each group, and shared, unmet needs (Hypothesis 1).2.Co-create a scientifically validated and evidence-based, patient-centered digital treatment for adolescents with chronic pain, involving all stakeholders: adolescents with chronic pain, parents, attending physicians, teachers, and health authorities. We expect that the digital treatment will be found user-friendly, and liked by all participants (Hypothesis 2).3.Evaluate DigiDOL-Ad in helping adolescents adjust to and manage chronic pain. We anticipate that adolescents with chronic pain using DigiDol-Ad will report statistically significant improvements in chronic pain and physical and psychosocial functioning after treatment, maintained at follow-up (Hypothesis 3).4.Assess whether the active involvement of parents and teachers, facilitated through dedicated companion websites, as change agents, that contribute to improved outcomes in adolescents with chronic pain. We hypothesize that adolescents whose parents and teachers actively engage with the digital treatment will experience greater improvements in pain management and quality of life compared to those with less engaged support (Hypothesis 4).

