In this study, the sample will include adolescents with chronic pain and one of their parents. Based on a within-subjects repeated measures ANOVA with three time points (baseline, post-treatment, and 3-month follow-up), we will use GPower (version 3.1.9.7) to calculate the required sample size. We set a small effect size (f = 0.10), with a two-tailed alpha of 0.05 and power of 0.80. For the calculation, the following parameters were assumed: number of measurements = 3 (baseline, post-treatment, and 3-month follow-up), correlation among repeated measures = 0.5, and nonsphericity correction epsilon = 1. This calculation indicated that a sample of *N* = 163 dyads would be sufficient. However, in order to prevent attrition issues, we will be recruiting a minimum of 195 dyads -minimal attrition is expected based on prior studies on digital treatments with similar populations (37). Recruitment is expected to proceed at a rate of approximately 5 participants per month, based on projections from similar previous studies [e.g., (30)]. To account for potential variability, we conservatively estimate a recruitment rate of 2 adolescents per month per hospital. With 8 hospitals participating, this would result in enrolling the required sample of 352 participants within 22 months. An additional 5 months will be allocated for participants to complete the treatment (approximately 8 weeks, as previously described) and the 3-month follow-up, bringing the total duration for recruitment, enrollment, and follow-up to 27 months.

In order to ensure that the target sample size is reached in the evaluation study, the following strategies will be implemented: (a) using clear and engaging messages (i.e., developing age-appropriate, visually appealing recruitment materials, like posters, flyers, or videos to be shared by hospitals and healthcare professionals); and (b) highlighting the benefits of participation, such as improving their own pain management and contributing to advancements in adolescent healthcare. Moreover, we will offer both monetary and non-monetary incentives (i.e., certificates of participation and feedback on their progress). To enhance participant retention and ensure completion of follow-ups, we plan to implement personalized reminders. These reminders will be delivered via app notifications, SMS, or email, and will serve to notify participants of upcoming tasks or scheduled follow-up activities.

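### Hypothesis 3 claims a benefit that is maintained at follow-up, but the only designated and powered test is an omnibus time F that passes equally often whether the benefit is held or fully lost

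*Protocol article*

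**What the plan says.** Section 1.1 (Objectives) states Hypothesis 3 in two parts: adolescents using the app will show "statistically significant improvements in chronic pain and physical and psychosocial functioning after treatment, maintained at follow-up". The first part concerns T2 against T1. The second concerns whether the gain is still there at T3.

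Section 2.3 (Participants) bases the sample size on one test: "Based on a within-subjects repeated measures ANOVA with three time points (baseline, post-treatment, and 3-month follow-up"). The inputs are given: "We set a small effect size (f = 0.10), with a two-tailed alpha of 0.05 and power of 0.80", with "correlation among repeated measures = 0.5, and nonsphericity correction epsilon = 1". The result is 163 dyads, and at least 195 are to be recruited to cover attrition.

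Section 2.5 (Data analysis) makes the same test the analysis of effect: "To study intervention effects, we will perform repeated measures ANOVAs, as described in section 2.3". Partial eta squared is its effect size. Individual visit comparisons enter through a single clause, "In cases where pairwise comparisons are conducted", which says only that Cohen's d will then be given. No contrast is named, no criterion for maintenance is set, and no contrast is powered.

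**The concern.** A three-level time F has one null hypothesis, that the means at T1, T2 and T3 are all equal. Rejecting it does not show that T2 is better than T1, and it says nothing specific about T3. A gain at T2 that has vanished by T3 is a departure from equality just as a lasting gain is. The test the protocol designates therefore cannot by itself support the maintenance half of Hypothesis 3.

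Two things are at stake. A significant F together with a good T2 mean could be taken as support for the whole hypothesis although T3 is back at baseline. And the stated 80% power may be read as the chance of confirming Hypothesis 3, when it is the chance of a significant F. Section 3.2 makes a future randomised trial depend on positive results here, so what counts as positive should match what is claimed.

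**Working it through.** **Inputs** (all from section 2.3): f = 0.10; m = 3 visits; correlation ρ = 0.5; ε = 1; two-sided α = 0.05; N = 163; recruitment minimum 195.

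**1. Reproduce the plan's N.** For a one-group within-subjects ANOVA, λ = N·m·f²·ε/(1 − ρ), with df1 = m − 1 and df2 = (N − 1)(m − 1).
- N = 163: λ = 163 × 3 × 0.01/0.5 = 9.78, df = 2 and 324, power 0.8024.
- N = 162: power 0.7998.

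So 163 is the smallest N with 80% power for the omnibus F. The arithmetic is right.

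**2. What f = 0.10 means in visit means.** f is the standard deviation of the three means in SD units. Take a common step d, with positive values as improvement.
- Held, (0, d, d): squared deviations from the mean are 4d²/9, d²/9 and d²/9. Their average is 2d²/9.
- Fully lost, (0, d, 0): squared deviations are d²/9, 4d²/9 and d²/9. Their average is again 2d²/9.

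Both patterns give f = d√(2/9). Setting f = 0.10 gives d = 0.10/√(2/9) = 0.212 SD in each case. Same f, same λ, same power: 0.8024 for both.

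**3. Power of the contrasts that address the hypothesis.** With ρ = 0.5 the SD of a change score is √[2(1 − 0.5)] = 1 SD, so the standardised mean change is 0.212. The paired t noncentrality is 0.212 × √N.
- N = 163: 2.708, power 0.768 (two-sided 0.05).
- N = 195: 2.962, power 0.838.
- A single contrast needs N = 177 for 80%.

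**4. Both contrasts together.** Trials were simulated under the plan's correlation structure (20,000 or more per pattern). Each contrast was tested two-sided at 0.05, and significance in the improving direction was required.

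| Pattern | N analysed | Omnibus F significant | T2–T1 and T3–T1 both significant |
|---|---|---|---|
| Held | 163 | 0.80 | 0.64 |
| Fully lost at T3 | 163 | 0.80 | 0.02 to 0.03 |
| Held | 195 | 0.87 | 0.74 |

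The omnibus F does not distinguish the first two rows; the pair of contrasts does. Power of 80% for both contrasts needs roughly 220 to 225 analysed dyads (simulated 0.794 at 220 and 0.816 at 225).

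**The case against.** The strongest reply is that the plan would not stop at the F. Means and standard deviations will be reported and pairwise comparisons are foreseen. If a significant F were followed by unadjusted paired tests, both contrasts would come out in the improving direction in 0.638 of trials when the benefit is held and 0.023 when it is lost, almost the same as the contrasts alone. A condensed article may also leave the naming of contrasts to an analysis plan. This stands in part: a sensible analyst could reach the right reading. But the comparisons are conditional and unnamed, and a later analysis plan would not make the 80% in section 2.3 apply to them.

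Several stronger readings are tempting but not supported:
- A reader might infer that a worsening could be reported as success. The F does reject for a worsening of the same size, but so does any two-sided test, and the direction is plain from the means.
- A reader might infer that the sample size is miscalculated, or that section 2.3 promises 80% for the two-part claim. Neither is so. The 163 is correct, and the 80% is attached to the ANOVA.
- A reader might infer that ε = 1 or the planned multiple imputation invalidates the analysis. In section 2.3, ε = 1 is a sample-size input, not a commitment to an uncorrected F. Unequal visit spacing does not by itself breach sphericity, and pooling methods for multi-parameter tests exist.

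Sections 3.1 and 3.2 also present the study as one of feasibility, usability and associated effects, and concede that a single group cannot establish attribution. That limits the consequence, but Hypothesis 3 is still stated as a claim of statistical significance.

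**Conclusion.** The point holds as a mismatch between hypothesis and test. At N = 163 the designated F is significant with probability about 0.80 whether a 0.21 SD gain is held or wholly lost at T3, so it cannot show maintenance. The 80% belongs to that F only. For the two-part claim, power per outcome is about 0.64 at 163 analysed and 0.74 at 195. The latter applies only with no attrition, whereas the extra dyads are recruited to cover attrition.

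These figures assume the plan's f, correlation and sphericity, an equal shift at T2 and T3, one outcome at a time, two-sided 0.05 tests, and maintenance read as T3 still better than T1. One-sided tests at 0.05 would give about 0.85 for one contrast and 0.76 for both at 163, but section 2.3 specifies a two-tailed alpha. Reading maintenance as no loss from T2 to T3 would need a margin, which the article does not give.

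This should be changed, but it does not undermine the study.

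**What to change.** In section 2.5, for outcomes that adolescents report at T1, T2 and T3 (such as pain intensity and pain interference), make two contrasts the test of Hypothesis 3: T2–T1 first, then T3–T1 only if the first is significant in the improving direction. Test each two-sided at 0.05; within an outcome the fixed order needs no alpha adjustment. Report each mean change with its 95% confidence interval, and keep the omnibus F and partial eta squared as descriptive. Paired contrasts on the imputed data are enough; a mixed model with time as a factor is an option, not a requirement.

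Exclude two groups of outcomes from this rule. Global impression of change has no baseline value, and the parent outcomes are not collected at T3.

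In section 2.3, state that 80% power refers to the omnibus F only, and add the power per outcome: about 0.77 for a single contrast and 0.64 for both with 163 analysed, or 0.84 and 0.74 if all 195 are analysed, assuming an equal 0.21 SD shift at T2 and T3.

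The cost is revised wording and a less favourable stated power. No extra data, visits or participants are needed unless the team wants 80% for the two-part claim, which would take roughly 220 to 225 analysed dyads.

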## Discussion

3

### Study significance

3.1

The overarching objective of this project is to help reduce pain impact and improve funtioning in adolescents with chronic pain by empowering them (and their families) to better adjust and cope with chronic pain related problems thorough the digital treatment that we will develop.

One of the major challenges facing the health system is the increasing demand from individuals with non-communicable chronic diseases. Research indicates a significant rise in the prevalence of chronic pain among adolescents (2). Moreover, several of the factors that are contributing to this increase are modifiable by psychosocial treatments [e.g., obesity, quality of sleep; (53–56)]. Therefore, an innovative digital psychosocial treatment based on proven, data-driven strategies that patients can access at their convenience could create significant positive impact across multiple dimensions.

From a scientific and technical perspective, the results from this project will have a ground-breaking positive effect on how we think about and treat adolescents with chronic pain. That is, the project will help to improve our understanding of the needs of all the interested stakeholders (i.e., adolescents with chronic pain, their parents, healthcare professionals, and their teachers) in relation to the management of chronic pain. In addition, it will also provide valuable insights into how the digital treatment can be made more appealing for integration into mainstream healthcare procedures. Moreover, by evaluating DigiDOL-Ad in real-world settings, we will gather essential data on the digitally delivered psychosocial-based treatment to support adolescents in managing chronic pain. Currently, there is a significant lack of data on effective remotely delivered treatments for this group (57). This can deepen the understanding of chronic pain mechanisms and its management in adolescents, informing future therapeutic approaches. Digital treatments can reach adolescents in underserved or remote areas where access to specialized pain management services is limited. Therefore, DigiDOL-Ad, by reducing geographical and financial barriers, will also help promote equitable healthcare access. Although this initial phase focuses on feasibility and usability, our future randomized controlled trial (RCT) will enable us to quantify the intervention's broader impact, including potential healthcare cost savings and the number of adolescents who could benefit from this approach.

As described previously, we will develop a website for teachers with resources and information to assist students with chronic pain. Chronic pain can impact academic performance, attendance, and overall school functioning (8, 58, 59). Educators can play a crucial role in supporting students with chronic pain (60), yet they often lack the necessary resources and knowledge to effectively manage these students' unique needs (61–63). Developing a dedicated website with comprehensive resources and information can bridge this gap, offering numerous advantages for educators and students alike. Such a platform can help reduce absenteeism, improve communication between teachers, students, and their families, and provide guidance on appropriate attitudes and responses to chronic pain. By equipping educators with the right tools, we could help create a more supportive and understanding school environment for students with chronic pain.

The impact of this digital treatment is expected to be significant at both structural and economic levels. Socially, the study findings may prompt a shift in healthcare practices, reinforcing that chronic pain is not solely a physical condition and advocating for collective responsibility in health management.

Economically, chronic pain poses a substantial public health challenge with significant direct and indirect costs for families and society (64, 65). Implementing this digital treatment could thus reduce the economic burden of chronic pain on the healthcare system. For example, if found to be effective, widespread use and prescription of this digital treatment could significantly reduce the number of patients requiring hospital visits. Additional cost savings would arise from reduced direct expenses (e.g., fewer complementary tests, reduced hospital personnel time) and indirect expenses (e.g., fewer missed workdays for families). Furthermore, the economic impact of these outcomes may stimulate further research and the development of new therapeutic procedures, potentially generating new employment opportunities. Our current study primarily focuses on establishing the feasibility, usability and associated effects of using the digital treatment, a comprehensive economic evaluation will be undertaken in a subsequent phase. This future RCT will provide detailed figures on the direct and indirect costs of chronic pain and quantify the potential cost savings that could be achieved by implementing this digital treatment, thereby reducing the economic burden on the healthcare system.

### Limitations

3.2

The key challenges anticipated in this project are related to (1) recruitment and inclusion of participants in the different studies, due to abandonment of a clinician/chronic pain program, and the difficulty to involve stakeholders in the FGs and usability studies; (2) privacy and data protection issues; (3) as a digital intervention, potential technical difficulties or poor usability could affect participants engagement; and (4) the content on companion websites for parents and teachers might be misunderstood, leading to unintended consequences. The mitigation actions (*contingency plan*) addressed to solve recruitment issues are as follows, depending on the causes: (a) monitoring constantly the involvement of clinicians, having a close and continued relationship with them (in relation to this, we have planned to send monthly updates to clinicians, and award a prize to the program providing the highest number of referrals), and (b) the Principal Investigator, in ongoing meetings with all stakeholders, will inform them on the project to raise interest and gain trust in the outcomes of the research proposal. In relation to (2) privacy data issues, we plan that the data collected during the implementation process will not leave the local secure networks where the data will be hosted at the university premises. Moreover, in relation to technical and usability issues, we have planned iterative usability testing phases and will provide dedicated technical support to identify and resolve any issues promptly. Finally, in relation to misinterpretation of information, the content will be developed in consultation with experts, and clear guidelines for interpretation and use will be provided.

Finally, another limitation of this project is the use of a single-group design to study the treatment. Without a control group for comparison, it is challenging to determine whether the observed outcomes are genuinely attributable to the treatment or influenced by external factors such as the placebo effect, natural progression of the condition, or other variables. If the evaluation study demonstrates positive results, a randomized controlled trial will be conducted in the future to validate and strengthen the findings.
